## Abstract

**Background:**

The gut microbiota is an important modulator of immune, metabolic, psychological and cognitive mechanisms. Chemotherapy adversely affects the gut microbiota, inducing acute dysbiosis, and alters physiological and psychological function. Cancer among young adults has risen 38% in recent decades. Understanding chemotherapy’s long-term effects on gut microbiota and psycho-physiological function is critical to improve survivors’ physical and mental health, but remains unexamined. Restoration of the gut microbiota via targeted therapies (e.g. probiotics) could potentially prevent or reverse the psycho-physiological deficits often found in young survivors following chemotherapy, ultimately leading to reduced symptom burden and improved health.

**Methods:**

This longitudinal study investigates chemotherapy induced long-term gut dysbiosis, and associations between gut microbiota, and immune, metabolic, cognitive and psychological parameters using data collected at < 2 month (T1), 3–4 months (T2), and 5–6 months (T3) post-chemotherapy. Participants will be 18–39 year old blood or solid tumor cancer survivors (*n* = 50), and a healthy sibling, partner or friend as a control (*n* = 50). Gut microbiota composition will be measured from fecal samples using 16 s RNA sequencing. Psychological and cognitive patient reported outcome measures will include depression, anxiety, post-traumatic stress disorder symptoms, pain, fatigue, and social and cognitive function. Dual-energy X-ray Absorptiometry (DXA) will be used to measure fat and lean mass, and bone mineral concentration. Pro-inflammatory cytokines, C-reactive protein (CRP), lipopolysaccharide (LPS), serotonin, and brain derived neurotrophic factor (BDNF) will be measured in serum, and long-term cortisol will be assayed from hair. Regression and linear mixed model (LMM) analyses will examine associations across time points (T1 – T3), between groups, and covariates with gut microbiota, cognitive, psychological, and physiological parameters.

**Conclusion:**

Knowing what bacterial species are depleted after chemotherapy, how long these effects last, and the physiological mechanisms that may drive psychological and cognitive issues among survivors will allow for targeted, integrative interventions to be developed, helping to prevent or reverse some of the late-effects of treatment that many young cancer survivors face. This protocol has been approved by the Health Research Ethics Board of Alberta Cancer Committee (ID: HREBA.CC-19-0018).

## Background

The digestive tract is the most densely colonized microbial ecosystem in the body. The bacteria that make up the majority of this ecosystem (in addition to fungi, viruses and archaea) are important for immune, metabolic, psychological and cognitive function. A disruption in the microbiota, termed dysbiosis may induce aberrant neurophysiological function and behaviour [1], such as increased anxiety and depressive behaviour [2] as well as impaired immune function characterized by increased systemic inflammation in humans and rodent models [3, 4]. Dysbiosis-induced systemic inflammation can independently and bidirectionally activate or exacerbate stress circuits, most notably the hypothalamic-pituitary-adrenal (HPA)-axis, via the vagus nerve [2, 5].Cancer treatments, especially chemotherapy, can drive microbial dysbiosis in the gut [6], alter immune, metabolic and HPA-axis function [7], as well as cause psychological and cognitive perturbations both acutely and, potentially in the longer-term [8, 9].

The incidence of cancer among young adults has risen nearly 40% in recent decades [10]. Early adulthood is an important period for psychological and cognitive development, which is influenced by biological and environmental factors, including the gut microbiota [11]. Understanding chemotherapy’s long-term effects on the gut microbiota and subsequent relationships with immune, metabolic, psychological and cognitive outcomes is of critical importance in order to improve young adult cancer survivors’ physical and psychosocial health, but remains unexamined. Therefore, based on the following model (Fig. 1), we plan to investigate whether chemotherapy treatments are related to long-term gut microbiota dysbiosis, and subsequent associations with immune, metabolic, psychological and cognitive outcomes.

**Fig. 1 Fig1:**
[figure not shown]
Chemotherapy Driven Dysbiosis of the Microbiota-Gut-Brain Axis. The Chemotherapy Driven Dysbiosis of the Microbiota-Gut-Brain Axis model posits that chemotherapy given to young cancer patients induces long-term gut dysbiosis, increasing intestinal permeability (i.e. “leaky gut”), which allows bacterial toxins, such as lipopolysaccharide (LPS), to enter the blood stream. This subsequently leads to systemic inflammation via increases in pro-inflammatory cytokines, especially IL-6, IL-1b, and TNF-a, and C-reactive protein, as well as dysregulation of the HPA-axis. This creates a feedback loop in which inflammatory mechanisms trigger the stress response to increase systemic cortisol, feeding back into the immune system to exacerbate levels of inflammation. Gut microbiota dysbiosis and dysregulation of the immune system and HPA-axis attenuate levels of serotonin (5-HT) and brain derived neurotrophic factor (BDNF), which then work in tandem to induce changes in psychological and cognitive function, including increased symptoms of anxiety and depression (i.e. “sickness behaviours”), pain, fatigue, and social and cognitive deficits. Finally, gut dysbiosis, immune, and HPA-axis dysregulation may also augment patients’ vulnerability to increased adipose tissue, and subsequent overweight and obesity, further compromising their health

### Cancer in young adults

The incidence of cancer among young adults has dramatically increased in recent decades [10], with over 8000 young Canadians diagnosed annually [12]. Between 1992 and 2013 the incidence of cancer has increased among young Canadian’s aged 15 to 29 by 18.2, and 11.9% among 30 to 39 year olds [12]. Considering their age at diagnosis, young adults experience unique personal, physical, and socioeconomic challenges throughout their cancer experience [12, 13]. As most young adult survivors are exposed to toxic therapies (e.g. chemotherapy) many will face years of chronicity living with treatment-related physical and psychosocial side-effects. For instance, Asher [14] reports that executive functioning, attention, concentration, processing speed, reaction time, motor speed and dexterity were the cognitive domains most frequently associated with chemotherapy induced cognitive impairment in all cancer populations. Additionally, Seitz et al. [15] examined the prevalence of posttraumatic stress, depression and anxiety among young adult survivors (*n* = 820) of adolescent cancer with a mean current age of 30.4 years [15]. They found that 90.5% cancer survivors had received chemotherapy, and 22.4% reported clinical symptoms of posttraumatic stress, anxiety and/or depression compared to only 14.0% of controls [15]. Posttraumatic stress symptoms in both male and female survivors were found to be more than three times that of controls [15]. Furthermore, female survivors reported symptoms of depression and anxiety significantly more often than controls, and 24.3% of the survivors met DSM-IV criteria for at least one mental disorder, relative to only 15.3% of the controls [15]. Indeed, the increased prevalence of young adult cancers in conjunction with the improved survival rates has resulted in a large group of survivors facing years of chronicity, unique challenges, and specific needs emerging from their cancer experience.

### Chemotherapy and gut microbiota

While the detrimental effects of chemotherapy on psychosocial and cognitive function are established, evidence for the underlying physiological mechanisms and system interactions that drive the psychological and cognitive impairments remains limited. The gut-brain axis refers to a bidirectional communication system within an organism that enables gut microbes to communicate with the brain and vice versa via neural, endocrine, immune and metabolic pathways [4, 16]. The role of the gut-brain axis in the context of the young adult is a critical consideration, since environmental toxins can interfere with normal development, potentially increasing individuals’ risk for developing psychiatric disorders such as depression and anxiety, which typically develop during adolescence and young adulthood.

Chemotherapy has been shown to adversely affect the gut microbiota in both pediatric and adult cancer cohorts. For example, Huang et al. [17] investigated changes in gut microbiota among 36 children with acute lymphoblastic leukemia (ALL) before and after receiving high-dose methotrexate chemotherapy, finding that the total gut microbial content in fecal samples decreased by 29.6%, relative to healthy controls, with significant reductions in Bifidobacteria*, Lactobacillus* and *E. coli* [17]. Furthermore, using a pre-post-measure design, Montassier et al. [18] examined 28 adult non-Hodgkin’s lymphoma patients treated with chemotherapy to assess the functional mechanisms of the gut microbiota in mediating the pathophysiology of mucositis. Mucositis is a condition characterized by painful inflammation and ulceration of the mucous membranes lining the digestive tract, affecting 70% of patients following chemotherapy [18, 19]. Significant decreases in Firmicutes and Actinobacteria, and increases in the abundance of Proteobacteria were observed alongside a reduced capacity for nucleotide, energy and vitamin metabolism, suggesting that chemotherapy induces severe compositional and functional imbalance in the gut microbiome that is associated with gastrointestinal mucositis [18]. While recent research demonstrates that chemotherapy is acutely associated with dysbiosis, research has not yet examined whether these effects persist in the longer-term (i.e. over months) following the cessation of chemotherapy. Therefore, as part of this study we will conduct a novel examination of the longer-term effects of chemotherapy on gut microbiota up to 6-months post-chemotherapy.

### Gut microbiota, immune function, the HPA-axis and chemotherapy

The gut-brain axis exerts regulatory effects on immune function and behaviour. Indeed, previous research has found that under certain conditions the protective epithelial layer in the gut can become compromised leading to increased intestinal permeability and consequently increased systemic circulation of the bacterial endotoxin, lipopolysaccharide (LPS), a component of the cell wall of Gram-negative bacteria [11, 20]. This “leaky gut” results in a peripheral inflammatory immune response, such that systemic levels of pro-inflammatory cytokines are increased [20], inducing sickness behaviours [21].

The potential for gut microbiota to affect the immune system and inflammatory mechanisms is a critical consideration in the context of anxiety and depression, as inflammation has been implicated as a driving factor in depressive illness [3, 22]. Behaviours indicative of sickness include lethargy, depression, anxiety, anorexia, social withdrawal and isolation, and have consistently been associated with augmented levels of pro-inflammatory cytokines, especially tumour necrosis factor alpha (TNF-α), interleukin 6 (IL-6), and interleukin 1 beta (IL-1ß) [21]. Additionally, studies involving Interferon alpha (INF-α) treatment for melanoma patients often report the development of cytokine induced depressive symptoms and sickness behaviours following INF-α treatment [23].

The HPA-axis may also play a role in mediating gut-brain axis functions. Previous studies have shown that gut bacteria can activate stress circuits via the vagus nerve [2], which modulates gut-brain axis function, subsequently affecting behaviour [5]. Corticotrophin releasing factor (CRF), a stress-related neuropeptide, is highly associated with gut-brain axis functioning [24]. Furthermore, results from human and animal studies have found that increased systemic inflammation (e.g. augmented pro-inflammatory cytokines from endotoxemia) is associated with increased levels of adrenocorticotropic hormone (ACTH) and cortisol, further implicating the role of immune function in moderating HPA-axis function [25]. As evidence continues to accumulate demonstrating that the gut-brain axis contributes to physiological function and affective behaviour related to the HPA-axis and immune system, it is important to consider the potential bi-directional communication between these systems, particularly in the context of disease.

Chemotherapy has been associated with increased intestinal wall permeability, mucositis, and the onset of a systemic inflammatory immune response, dysregulation of the HPA-axis, and subsequent manifestation of sickness behaviours [11, 20, 21]. Gut microbiota may play a role in mediating such effects [7]. Moreover, in addition to adversely affecting the gut microbiota, chemotherapy-induced mucositis is also associated with significant elevations in systemic pro-inflammatory cytokines, especially IL-1ß and IL-6 [26], which are accompanied by increased symptoms of pain, anxiety, and depression [27]. As such, the potential disruption of normal physiological and psychological development among young cancer survivors and the role of gut microbiota in moderating such changes is of particular concern, as many survivors face lifelong health challenges following a cancer experience, which is why these immune and metabolic components have been included within our study.

### Gut microbiota, and psychological and cognitive function

Gut microbiota dysbiosis has been implicated in cognitive and psychological deficits. Previous studies demonstrate that alterations in gut microbiota can affect both anxiety and depressive behaviour in animals and humans [2, 28–31]. Neurotransmitter dysregulation is widely implicated in depressive illness, and certain neurotransmitters including serotonin (5-HT), dopamine, GABA (gamma-Aminobutyric acid), and noradrenalin, are affected by the gut microbiota [4, 32]. This is an important consideration given that neurotransmitters, especially serotonin as it participates in mood regulation, are implicated in the neurological dysregulation observed in depressed patients [33] and cancer survivors frequently experience comorbid depression following a cancer experience [15]. Furthermore, a small but growing body of pre-clinical evidence suggests that the gut-brain axis also plays a role in cognitive function, including spatial learning and working memory [34], and alterations in brain derived neurotrophic factor (BDNF) expression in regions of the brain that are associated with specific cognitive functions (e.g. the hippocampus, which is involved in learning and memory) [34, 35].

While the majority of evidence stems from animal research, some human studies have also shown associations between the gut microbiota, and psychological and cognitive function**.** For instance, Prehn-Kristensen et al. [36] investigated the gut microbiota composition of 14 male attention deficit hyperactivity disorder (ADHD) patients compared with healthy male controls, and found that alpha diversity of ADHD patients was significantly decreased, and augmented levels of *Bacteroidaceae*, and both *Neisseriaceae* and *Neisseria spec*. Were identified as potential biomarkers for the ontogeny of juvenile ADHD [36]. Additionally, Naseribafrouei et al. [37] examined associations between human fecal microbiota and depression in 55 adults (37 patients versus 18 controls), finding that Bacteroidales were overrepresented, while *Lachnospiraceae* species were underrepresented among depressed patients. Additionally, the *Oscillibacter* genus, of which valeric acid is the main metabolic end product and a homolog of the neurotransmitter GABA, a neurotransmitter implicated in major depressive disorder, was also correlated with depression [37].

Furthermore, in a triple-blind, placebo-controlled, randomized, pre- and post-intervention study with 40 healthy participants, Steenbergen et al. [29] investigated the effects of a multispecies probiotic versus a placebo control on cognitive reactivity to sad mood. Participants who received the 4-week probiotic intervention showed a significant attenuation in overall cognitive reactivity to sad mood, which appeared to be a function of reduced rumination and aggressive thoughts [29]. Finally, Hilimire et al. [28] conducted a cross-sectional study with 710 young adults to examine whether consumption of fermented foods, which contain probiotics, interacts with neuroticism to predict social anxiety symptoms, using self-reported measures of fermented food consumption, neuroticism, and social anxiety [28]. For individuals reporting high traits of neuroticism, greater consumption of fermented food was associated with fewer symptoms of social anxiety, suggesting that fermented foods containing beneficial probiotic bacteria may exert protective effects against social anxiety symptoms for young adults with higher trait neuroticism [28]. Although the underlying mechanisms mediating these cognitive-behavioural effects remain to be elucidated, it is plausible that alterations in gut microbiota resulting from dietary supplementation with health promoting bacteria play a role.

Chemotherapy has been associated with cognitive and psychological impairments [14, 15]. For example, Prasad et al. [38] examined associations between neurocognitive dysfunction and psychosocial outcomes on the achievement of social milestones among adult survivors of adolescent and early young adult (AeYA) cancer who had been diagnosed between 11 to 21 years of age. Relative to healthy siblings, AeYA survivors’ were more likely to experience neurocognitive dysfunction in domains related to task efficiency, emotion regulation, and memory, were less likely to be married or employed, and reported greater levels of emotional distress characterized by anxiety, somatization, and depression [38]. Given this, the potential role of gut microbiota in mediating or moderating chemotherapy’s effects is an important direction for novel investigation. Such knowledge will help us to better understand the ontogeny of cognitive and psychological deficits in young cancer survivors, while also presenting new opportunities for targeted interventions perhaps via prebiotic and/or probiotic supplementation of key health promoting bacteria that may be depleted following chemotherapy.

### Cancer, gut microbiota and obesity

Findings regarding associations between gut microbiota and obesity also hold implications related to body composition among young adult cancer survivors who tend to be more overweight and obese relative to healthy peers. For example, recent data from a sample of 49 young adult survivors of adolescent cancer found that over 57% of these survivors were overweight or obese, which is higher than the national average [39], and consistent with previous research on obesity in adolescent and young adult (AYA) cancer survivors [40]. In human and animal studies, diet and/or antibiotic induced gut microbiota dysbiosis has been shown to play a strong role in the development of obesity [41–44]. Given the established link between obesity and gut microbiota dysbiosis [45], it is possible that chemotherapy may adversely affect metabolic processes mediated by the gut microbiota, resulting in an increased risk for young adult cancer survivors to become overweight or obese. However, additional research is needed to examine the potential relationship between chemotherapy, gut microbiota, and fat mass among young cancer survivors; a rationale for our inclusion of these elements in our study.

### Present study

#### The objectives of the present study are to investigate

i.Whether chemotherapy is related to long-term attenuation of gut microbiota alpha diversity (i.e. gut dysbiosis, and which species differ significantly between patients and healthy controls);ii.Associations between gut microbiota, body composition (i.e. fat mass and lean mass, body fat percentage, and bone mineral concentration), inflammatory cytokine biomarkers (IL-6, IL-1B, TNF-a, IL-10), C-reactive protein (CRP), lipopolysaccharide (LPS), serotonin (5-HT), brain derived neurotrophic factor (BDNF), and cortisol;iii.Associations between gut microbiota, and psychological and cognitive outcomes including anxiety, depression, PTSD symptoms, pain, fatigue, and social and cognitive functioning;iv.Relationships between demographic and clinical factors, gut microbiota, and physiological, psychological and cognitive outcomes for survivors.

We hypothesize that:
i.Chemotherapy will be associated with significant reductions in gut microbiota alpha diversity at all time points, and relative to healthy controls;ii.Gut dysbiosis will be associated with increased risk for overweight/obesity, elevated pro-inflammatory cytokines, CRP and LPS, reduced serotonin and BDNF, and augmented levels of cortisol in survivors;iii.Gut dysbiosis will be associated with increased anxiety, depression, PTSD symptoms, pain, fatigue, and social and cognitive deficits in survivors;iv.There will be relationships between certain clinical factors (e.g. mucositis, antibiotic use), gut microbiota alpha diversity, and physiological, psychological and cognitive outcomes.

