##### Sample size and power

Target sample sizes of at least *n* = 50 cancer survivors and *n* = 50 healthy controls were selected based on sample sizes from previous studies on gut microbiota in cancer patients [17, 18] and practical considerations given the timeline and availability participants. With this sample size (*n* = 100 total), a medium effect size for group differences (Cohen’s d = 0.5, estimated with a power of 0.80, alpha = 0.05) can be detected using a one-sided test of the primary hypothesis that cancer survivors will have lower alpha diversity relative to controls [46].

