### Demographics and clinical data

Clinical and demographic factors including current age, age at diagnosis, income, occupation, ethnicity, education, living arrangements, cancer diagnosis and treatments received, history of treatment related mucositis, current diet and exercise regimes, bowel habits, glucocorticoid medication, antibiotic, and probiotic use within the last 2 years, smoking, birth delivery mode (i.e. caesarian section vs. vaginal), and breastfeeding during infancy will be collected as these variables are known to impact the gut microbiota.

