### Procedure

Once identified, participants will be contacted by telephone or email to further verify inclusion and exclusion criteria, to obtain written informed consent, and schedule their first appointment. We will aim to assess participants at 3 different time points: < 2 months (T1), 3/4 (T2) and 5/6 (T3) months post chemotherapy, with healthy controls ideally being tested on the same day or within 5 days from when the patient is tested.

Participants will then receive a package via mail or in person, with instructions and materials for stool sample collection, and a link to fill out the self-report questionnaires, and demographic and clinical data online using REDCap. REDCap is a free, secure, browser-based application designed to support Electronic Data Capture for research studies provided through the Clinical Research Unit in the Cumming School of Medicine at the University of Calgary. Medical charts will also be accessed to confirm information regarding cancer diagnosis, treatment, glucocorticoid and antibiotic medication use, and mucositis.

Participants will be instructed to collect stool samples at home which can be stored in a freezer up to 3 days prior to their appointment, and to complete their online questionnaires prior to the appointment. On the day of their appointment, we will collect their stool sample from them. Participants will then be taken to have a hair sample collected for cortisol analysis (approximately 10 min), complete the cognitive task (i.e. the SART) on a computer (approximately 6 min), and complete their DXA scan (approximately 10 min), and have their blood drawn for serum biomarker analyses (approximately 10 min). This whole process should take approximately 45 min. Participants’ T2 and T3 month follow-up appointments will be scheduled at each subsequent visit and the procedure will be the same with respect to psychological and cognitive measures completed online, followed by their in person testing and biological sample collection. Participants will be provided a voucher for parking, and may choose from compensation in the form of either $30 at the end of the study or a pass to a fitness class after each appointment (they will have options to choose from in advance). If desired, participants will also receive a package with their individual results summarized and interpreted at the end of the study.

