### Data analysis

*Objective 1* will examine whether chemotherapy is related to long-term gut dysbiosis as indicated by reduced alpha diversity in patients relative to controls, and from time points 1 through 3. Gut microbiota alpha diversity will be evaluated with the Shannon and Chao1 indexes using QIIME. To further examine differences in bacterial composition between the groups, LEfSe (linear discriminant analysis effect size) will be used to evaluate differential abundance between patients and controls, allowing us to identify the key bacteria that contribute most to the chemotherapy group having different bacteria relative to healthy controls. Linear Mixed Modelling (LMM) analyses will be used to examine differences across time and between groups. Group (survivors vs. healthy controls) and time (T1 – T3) will be fixed factors and individual subject will be a random factor.

*Objective 2* will first test group differences in gut microbiota, cytokines, LPS, 5-HT and BDNF, cortisol, and body composition using LMM as described above. We will test the interplay between the physiological systems of our model by examining associations between the gut microbiota, cytokines, LPS, 5-HT and BDNF, cortisol, and body composition using univariate correlations. Then multivariate regression models regressing cytokines, cortisol and body composition on gut microbiota diversity will be conducted, including variables that showed significant univariate correlations in the modelling. Covariates included theoretically based on the literature will include type of cancer diagnosis (i.e. blood or solid tumor), history of mucositis, glucocorticoid medication, antibiotic, and probiotic use, birth delivery mode, and breastfeeding in infancy.

*Objective 3* will first test group differences in cognitive and psychological parameters, gut microbiota diversity, and levels of 5-HT and BDNF using LMM as described above. We will test the relationships between gut microbiota, 5-HT and BDNF, and cognitive and psychological parameters using univariate correlations. Then multivariate regression models regressing psychological and cognitive parameters on gut microbiota diversity will be conducted, including variables that showed significant univariate correlations in the modelling. Covariates included theoretically based on the literature will as specified in objective 2.

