## Discussion

Using the Microbiota-Gut-Brain Axis model and the biopsychosocial framework, this research aims to elucidate the long-term effects of chemotherapy on gut microbiota, and psychological, cognitive, metabolic, and immune outcomes in young adult cancer survivors. Moreover, this study will allow us to systematically explore and validate aspects the novel model proposed here; the Chemotherapy Driven Dysbiosis of the Microbiota-Gut-Brain Axis Model.

The design of this study is not without its limitations and we have taken steps to reduce potential confounds and bias. Although the sample size of this study is relatively small, it is comparable to other studies examining the effects of chemotherapy on gut microbiota, and taking into account feasibility, this sample size will produce adequate statistical power. Furthermore, while most studies typically require participants to have not taken antibiotics for at least 3 months prior to fecal collection, we have set the required time at 1 month. This is to account for the health status of the clinical population, tight timing between follow-up appointments, and to reduce potential attrition. Although colorectal cancers do frequently occur in young adults, we have chosen to exclude this specific diagnosis type from our sample as previous research suggests that specific changes in gut microbiota may be involved in the onset and/or progression of colorectal cancer [56, 57], and therefore present a potential confounding variable. Taking into consideration that the first data collection time point is very close to the final chemotherapy treatment, it is possible that hair sample collection may not be feasible for all patients, in which case hair samples may only be collected at time points 2 and 3 for some patients. However, this should still allow us to examine changes in cortisol over 3-4 and 5- 6 months post-chemotherapy since hair cortisol allows for retrospective cortisol quantification. Finally, as this novel study is exploratory in nature, we think that the methodological plan outlined will provide a rich and varied data set with which we will be able to answer our research questions. This knowledge will ultimately be used to inform future, larger studies and, most importantly, interventions.

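### A bowel diagnosis excludes controls but not survivors and no stated model term covers it, so the primary alpha-diversity contrast may partly reflect selection

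*Protocol article*

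**What the plan says.** The first hypothesis in the protocol article reads: "Chemotherapy will be associated with significant reductions in gut microbiota alpha diversity at all time points, and relative to healthy controls".

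The article prints both eligibility lists. Under the exclusion criteria for control participants, a diagnosis of irritable bowel syndrome/disease is a reason not to enrol. Under the exclusion criteria for survivors, the items are CNS or colorectal tumour, allogeneic transplant, pregnancy, recent antibiotics, and a cognitive or developmental delay that came before the cancer. No bowel syndrome or disease appears there.

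The section on demographics and clinical data lists "current diet and exercise regimes, bowel habits, glucocorticoid medication, antibiotic, and probiotic use within the last 2 years", among other items, but no bowel diagnosis. The Procedure section describes the chart review: "Medical charts will also be accessed to confirm information regarding cancer diagnosis, treatment, glucocorticoid and antibiotic medication use, and mucositis".

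For Objective 1, the Data analysis section says that group and time "will be fixed factors and individual subject will be a random factor". The covariates named for Objective 2, and carried to Objective 3, are cancer type and "history of mucositis, glucocorticoid medication, antibiotic, and probiotic use, birth delivery mode, and breastfeeding in infancy". They include neither a bowel diagnosis nor bowel habits.

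The sample size section rests on a "one-sided test of the primary hypothesis that cancer survivors will have lower alpha diversity relative to controls". The Discussion explains the shorter antibiotic window for survivors and the colorectal exclusion, but does not mention this difference between the groups.

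**The concern.** The controls are siblings, cohabitants or close friends. They stand in for what the survivors' microbiota would look like without cancer and chemotherapy. That works only if features unrelated to chemotherapy are allowed in, or kept out, to the same extent on both sides. Here a pre-existing bowel disorder is removed from the controls and left in the survivors. If such a disorder changes alpha diversity, the two groups would differ even if chemotherapy did nothing.

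The primary test is one-sided towards lower survivor diversity. If the disorder lowers diversity, the selection pushes in the direction that the test rewards. The Objective 1 model has no term that could separate this from a chemotherapy effect. Recruiting more participants under the same rules would not remove it.

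**Working it through.** **Inputs from the protocol article.** 50 survivors and 50 controls; Cohen's d = 0.5; one-sided test, "estimated with a power of 0.80, alpha = 0.05".

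**Inputs not in the document (assumed).** p, the share of enrolled survivors with a pre-cancer bowel diagnosis: 2% to 20%. g, the deficit in alpha diversity among them: 0.3 to 1.0 SD. In controls p = 0, by exclusion.

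**Step 1: the plan's own figure.** n per group = 2 × (1.645 + 0.842)² / 0.5² = 49.5, rounded up to 50. Power at 50 per group: the standard error of the difference in SD units is √(2/50) = 0.20, and Φ(0.5/0.20 − 1.645) = 0.804. The t test gives 0.799. The stated 0.80 reproduces, and this point does not affect it.

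**Step 2: the shift from selection.** With no chemotherapy effect, the survivor mean lies below the control mean by p × g.

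**Step 3: one-sided rejection rate with no chemotherapy effect.** Φ(p × g / 0.20 − 1.645).

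| p | g (SD) | Shift (SD) | Share of d = 0.5 | Rejection rate |
|---|---|---|---|---|
| 2% | 0.3 | 0.006 | 1.2% | 0.0532 |
| 2% | 1.0 | 0.020 | 4% | 0.0612 |
| 10% | 0.3 | 0.030 | 6% | 0.0675 |
| 10% | 1.0 | 0.100 | 20% | 0.1261 |
| 20% | 0.3 | 0.060 | 12% | 0.0893 |
| 20% | 1.0 | 0.200 | 40% | 0.2595 |

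These rates use the two-group comparison on which the sample size is based, with SD 1 in both groups. They do not simulate the mixed model.

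**Step 4: direction.** If g were zero there would be no shift. If g were negative (the disorder goes with higher diversity), the shift would work against the hypothesis and mask a real deficit.

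**Step 5: change over time.** A diagnosis that predates the cancer and shifts a survivor's diversity by a constant amount adds the same amount at T1, T2 and T3. It cancels in that survivor's own change, so the trajectory part of Objective 1 is largely untouched.

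**The case against.** The strongest reply is that the harm is hypothetical. The document does not say how common a pre-cancer bowel diagnosis is among these survivors, or that it lowers alpha diversity. That stands. A reader might infer from the unequal lists that part of any survivor deficit is produced by selection. The text supports only that it may be.

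A reader might also infer that bowel status goes unrecorded. That is too strong. Bowel habits are collected, the list is introduced as an inclusive one, this is a condensed article, and Objective 4 relates clinical factors to alpha diversity among survivors. But current bowel habits cannot date a disorder to before the cancer or tell it from an effect of treatment. An analysis within survivors also does not repair a comparison with controls. The mismatch is between two printed eligibility lists, so it is not detail left to another document.

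Controls are meant to be healthy, so some health exclusions on their side are natural. That explains the criterion but does not remove the bias from a contrast attributed to chemotherapy.

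The colorectal exclusion, made because such tumours "and therefore present a potential confounding variable", is only a partial parallel. The reason given there is that the microbiota may be involved in the onset or progression of that tumour. It is not a general rule about bowel conditions, and no reason is given for the bowel criterion in controls.

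Finally, it may be tempting to carry the bias over to the LPS and cytokine contrasts. The unequal selection applies to those comparisons too, but nothing in the document shows that a bowel diagnosis alters those markers.

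**Conclusion.** The point holds in conditional form. The exclusion applies to one group only, the diagnosis is not a listed data item, and the Objective 1 model has no term for it. As written, the primary survivor-control contrast is open to differential selection, and the stated plan has no means of showing how much.

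Under the assumed ranges the shift is about 0.006 to 0.20 SD, or 1% to 40% of the effect the study is sized for, with one-sided error of about 5% to 26%. The upper end needs both a 20% prevalence and a full 1 SD deficit. At 2% prevalence the error stays between 5.3% and 6.1%, which is negligible. Direction is as uncertain as size. The concern is confined to comparisons between groups and leaves the T1 to T3 change within survivors largely intact.

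**What to change.** 1. For survivors not yet enrolled, add the bowel criterion to the exclusion list, limited to diagnoses made before the cancer. The list already takes this form for cognitive or developmental delay. Bowel complaints that arose with treatment stay in, since they may be part of the effect under study.
2. For all enrolled survivors, record any bowel diagnosis and its date by a question in the online form, confirmed in the charts that are already being opened.
3. Specify, before the groups are compared, that the Objective 1 group contrast will be reported with and without survivors whose bowel diagnosis predates the cancer, as a sensitivity analysis. Making the restricted set the main result in an ongoing study would go further than needed.

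**Cost.** One line of eligibility text, one question, one extra analysis, and a few otherwise eligible survivors lost. The target of 50 per group does not change. The restricted analysis is slightly less precise: at the assumed extreme of 20% affected it would compare 40 with 50, and power for d = 0.5 would be Φ(0.5/√(1/40 + 1/50) − 1.645) = 0.76, against 0.80 with all 50.
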